**Standard package**	
Small-scale educational meetings	Workshop or skills training for perioperative key disciplines including assignments, role playing, own presentations, patient stories or discussion, and problem solving of hypothetical patient situations/case studies. Provided by an opinion leader within the field of patient safety or a highly respected colleague. Based on active participation in small groups: multi- or mono-disciplinary groups (i.e., per discipline, e.g., surgeons and recovery nurses separately). The content is based on the key constraints and the most important obstacles in applying the guidelines for a hospital (based on the results of the audit) and a brainstorming session during the training or pre-handed topics participants find important to discuss.
Audit and feedback	Feedback is based on the indicator measurement(s), structural observation, barrier analysis, and the TCI and HSOPS questionnaires. The feedback consists of a local paper report with the hospital’s own results, benchmarked, and presented in relation to all nine participating hospitals. The hospitals in the intervention phase receive this report shortly after a measurement period. The feedback report is presented and discussed with the key professionals in a meeting.
Structural observation	Observation by a trained expert of the pre-, per-, and postoperative trajectory of one surgical patient (on the ward, operation room, and recovery ward) based on a structured observation list. Feedback is based on the completed observation list. The hospitals receive the feedback immediately afterwards. Also, the structured observation list used is then made available to the hospital. In this way, the hospital is able to perform its own observations of the perioperative process.
Local embedding of the guidelines	Concrete and visible integration into and/or completion of a local protocol and/or checklist, for example, the adaptation of the guidelines in a local protocol; conducting audits (indicator measurements), structural observations, and visitation to monitor the implementation of the guidelines; the use of reminder systems (completing existing checklists based on the guidelines, if possible, new digital checklist may be installed in electronic patient records); decision support and feedback on the implementation of the protocol (using ICT); and incorporation of the guidelines in the clinical pathway, e.g., resignation letter to the general practitioner.

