### Outcome measures

Several outcomes are measured at the hospital (i.e., the cluster) and the patient levels (Table 3). The primary outcome measure is guideline adherence according to the PSIs as defined in the national indicator set. This set comprises nine indicators on the processes and structures of care [18]. Secondary (patient) outcomes are in-hospital complications (with particular attention to postoperative wound infections) and hospital mortality, as well as length of hospital stay (LoHS), unscheduled transfer to the intensive care unit (ICU), non-elective hospital readmission, and unplanned reoperation, which are derived from a maximum period of 30 days after the initial surgery.

**Table 3 Tab3:** **Methods and instruments for measuring the effects of a multifaceted implementation strategy to implement the Dutch national perioperative safety guidelines**

**Outcome variable**	**Data source (type of measurement)**	**Frequency of measurement and sample size per measurement**	**Moment of measurement**	**Unit of analysis**
**Primary outcome** (guideline adherence measured by an indicator set of nine process and structure indicators)				
Completion of the total STOP bundle (seven separate stop moments in the perioperative care process), % patients	Retrospective patient record review in the hospital information systems	4 (T0 (before), T1, T2, T3 (after) measurement) *N* = 1,800	−3 months, +4 months, +11 months and +18 months	Patient
Availability of a protocol on antibiotic use	Short questionnaire on the underlying items of the structure indicators	4 (T0 (before), T1, T2, T3 (after) measurement) *N* = 1	−3 months, +4 months, +11 months and +18 months	Hospital
Timely administration of antibiotic prophylaxis, % patients	Retrospective patient record review in the hospital information systems	4 (T0 (before), T1, T2, T3 (after) measurement) *N* = 1,800	−3 months, +4 months, +11 months and +18 months	Patient
Availability of a protocol on anticoagulant use	Short questionnaire on the underlying items of the structure indicators	4 (T0 (before), T1, T2, T3 (after) measurement) *N* = 1	−3 months, +4 months, +11 months and +18 months	Hospital
Availability of a protocol on responsibilities regarding maintenance of medical equipment	Short questionnaire on the underlying items of the structure indicators	4 (T0 (before), T1, T2, T3 (after) measurement) *N* = 1	−3 months, +4 months, +11 months and +18 months	Hospital

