Availability of a protocol on (performing) prospective risk analysis of medical equipment	Short questionnaire on the underlying items of the structure indicators	4 (T0 (before), T1, T2, T3 (after) measurement) *N* = 1	−3 months, +4 months, +11 months and +18 months	Hospital
Availability of OR regulations	Short questionnaire on the underlying items of the structure indicators	4 (T0 (before), T1, T2, T3 (after) measurement) *N* = 1	−3 months, +4 months, +11 months and +18 months	Hospital
Presence of a surveillance system for postoperative wound infections	Short questionnaire on the underlying items of the structure indicators	4 (T0 (before), T1, T2, T3 (after) measurement) *N* = 1	−3 months, +4 months, +11 months and +18 months	Hospital
Presence of a morbidity and mortality registration	Short questionnaire on the underlying items of the structure indicators	4 (T0 (before), T1, T2, T3 (after) measurement) *N* = 1	−3 months, +4 months, +11 months and +18 months	Hospital

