### Data sources

Information about the processes and outcomes of perioperative care are retrospectively derived from patient medical records in the participating hospitals by two researchers (YE and GB). The first 50 patients undergoing an initial elective surgery within the measurement period and who meet the inclusion criteria are selected from the hospital databases.

To measure the structure indicators of the national indicator set, the contact person in each hospital is invited to fill out a short questionnaire on the underlying items of the structure indicators on a dichotomous scale (yes/no).

Health-care providers in the concerning hospitals are invited to respond to two different questionnaires and additional background questions on gender, medical position, and years of experience in the current function and in the current hospital. The Team Climate Inventory (TCI) [33] and the Hospital Survey on Patient Safety Culture (HSOPS) [34] are used to analyze whether team climate and patient safety culture are determinants of guideline adherence. The TCI measures the climate of the various teams of health-care providers. Good team work is essential to provide proper and safe care [35-37]. The TCI is a valid, reliable, and discriminating self-report measure of the climate of a hospital team. The TCI is based on a four-factor theory of team climate for innovation and assesses the factors, vision, participative safety, task orientation, and support for innovation in 13 subscales [33]. To measure the patient safety culture, we use the HSOPS [34,38]. The HSOPS is a valid and reliable survey for assessing the patient safety culture in hospitals. It measures 12 dimensions of patient safety culture on the basis of ideas of unsafely designed care processes or systems that increase the likelihood of the occurrence of adverse events.

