### Process evaluation

A process evaluation, according to Hulscher et al. [42], will be performed during and after the intervention to investigate the feasibility of the implementation strategy and to gain insight into the impact of individual implementation activities on guideline adherence. For this purpose, we will document the different implementation activities and the participation level of the health-care providers in order to determine the correlation between the implementation effect (i.e., results of our implementation strategy on guideline adherence) and compliance to the implementation strategy (i.e., degree of implementation). For this, we use the framework of Hulscher et al. for describing the key features of an implementation of change intervention [43]. In this framework, attention is paid to features of the target group, features of the implementers, and the frequency and intensity of intervention activities [43]. Based on this framework, we describe the features of the intervention as performed in detail. The process evaluation will furthermore be based on a questionnaire for the contact persons and a questionnaire for the health-care providers to measure their experience with the implementation strategy. The survey will be emailed to those who have participated in an activity. We will also determine other factors that could have influenced adherence to the perioperative safety guidelines, such as local interventions in the hospitals, audits by the IGZ, other scientific studies in this field conducted in the participating hospitals, and possible confounding factors and barriers for guideline adherence like changing registration systems in the hospitals or merging hospitals.

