With respect to the limitations of the study, the power of the stepped wedge cluster randomized trial design decreases if the treatment gradually reaches its expected effect after one or more time intervals after the intervention [22]. The greater the delay in the intervention effect, the greater the loss of power. This can be a problem in the third group of hospitals as the effect measurement is conducted immediately after the implementation phase (the last group starts with the implementation activities after T2). It is therefore important to make the time intervals sufficiently long so that the full intervention effect is realized in a single interval. The power can also be partly, but not completely, restored by adding additional measurement periods onto the end of the trial. Another limitation of this study is the costs of the frequent data collection. If the necessary data are not easy to collect and time-consuming, the cost of data collection is substantial. A further limitation is due to the fact that our sample size is calculated for the primary outcome measure. Power may be too low to draw conclusions about the effect of guideline adherence on perioperative patient safety. Blinding of the intervention is not possible as the trial is designed to evaluate an implementation intervention to change professional behavior in the real hospital setting. Outcomes assessment was not blind either, but as indicators are rather objective (e.g., is a protocol for anticoagulant use available or not), it is unlikely that they are influenced by the assessment.

Overall, knowledge of the results of this study will improve the implementation success of the perioperative guidelines. It is expected that better adherence to the perioperative safety guidelines will improve the safety of perioperative care.

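### The Discussion calls the indicators objective, but seven of nine primary indicators are self-reported with no check described, and recorded STOP-bundle completion can rise through better recording alone

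*Protocol article*

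**What the plan says.** All references are to the protocol article.

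- **Blinding (Discussion, limitations).** "Outcomes assessment was not blind either". Influence on the outcome is nevertheless judged unlikely, "as indicators are rather objective (e.g., is a protocol for anticoagulant use available or not".
- **Primary outcome (Outcome measures).** "This set comprises nine indicators on the processes and structures of care". Table 3 gives the source for seven of them as "Short questionnaire on the underlying items of the structure indicators". For the other two, STOP-bundle completion and timely antibiotic prophylaxis, it is "Retrospective patient record review in the hospital information systems".
- **Who answers the questionnaire (Data sources).** "the contact person in each hospital is invited to fill out a short questionnaire on the underlying items of the structure indicators", on a yes/no scale.
- **What the strategy may change (Table 2, standard package, local embedding of the guidelines).** Among the examples are reminder systems, explained as "completing existing checklists based on the guidelines, if possible, new digital checklist may be installed in electronic patient records".
- **Checks described.** Analysis covers out-of-range, inconsistent or missing data. The Discussion adds that the same researchers check registry and medical-record data, an independent researcher checks data entries, and an external advisory board looks at design and integrity.
- **Recording changes (Process evaluation).** Factors to be determined include "possible confounding factors and barriers for guideline adherence like changing registration systems in the hospitals or merging hospitals".

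**The concern.** The objectivity argument is the article's only stated reason for setting aside bias from unblinded assessment of the primary outcome. It does not match the data sources.

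Whether a protocol exists is an objective fact. What is measured, however, is an answer given by someone in the hospital receiving the strategy. That hospital knows its phase, and its indicator results are fed back and benchmarked against all nine hospitals.

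The STOP bundle raises a different problem. It requires all seven stop moments, so one stop that was performed but not recorded can fail the whole bundle. If the strategy adds or completes a checklist in the record, the measuring instrument changes at cross-over. Part of a rise in recorded completion could then reflect better recording rather than more stop moments performed. The same measure feeds the adherence-outcome analysis and the output side of the economic evaluation.

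**Working it through.** **1. Count the indicators (Table 3).**

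| Source | Indicators | Number |
|---|---|---|
| Questionnaire to contact person | antibiotic protocol; anticoagulant protocol; equipment maintenance; equipment risk analysis; OR regulations; wound-infection surveillance; morbidity and mortality registration | 7 |
| Patient record review | STOP bundle; timely antibiotic prophylaxis | 2 |

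7 + 2 = 9, which agrees with the stated total. The anticoagulant protocol, the Discussion's example of objectivity, is in the questionnaire row.

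**2. Set the described checks against the sources.** Source checking names registries and medical records. Entry checking tests transcription. Data cleaning tests range, consistency and missingness. None of these, as described, tests whether a questionnaire 'yes' is true.

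**3. Can the analysis separate recording from care?** The model has fixed time effects and compares control with intervention cells. A recording change made by the strategy begins when the hospital crosses over, so it follows the same 0/1 pattern as the treatment indicator in Table 1. Period effects remove only what is common to all hospitals in a round.

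**4. Possible size for the STOP bundle.** The article gives no figure for recording completeness, so these inputs are assumptions: true completion *q* = 60% throughout, recording of completed bundles rising from *r* to 100%, and every hospital changing its forms. Apparent gain = *q* × (1 − *r*).

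| *r* before | Recorded before | Recorded after | Apparent gain |
|---|---|---|---|
| 95% | 0.60 × 0.95 = 57% | 60% | 3 points |
| 90% | 0.60 × 0.90 = 54% | 60% | 6 points |
| 80% | 0.60 × 0.80 = 48% | 60% | 12 points |

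If only a third of hospitals change forms, spread evenly over the groups, the average gain is about a third of this: 1, 2 or 4 points.

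**5. How often would such a shift alone reach significance?** Use the Hussey and Hughes variance with I = 9 hospitals, T = 4 rounds and 50 patients per hospital and round. From Table 1:

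- U = 18
- W = 0² + 3² + 6² + 9² = 126
- V = 3 × (3² + 2² + 1²) = 42

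Var = Iσ²(σ² + Tτ²) / [(IU − W)σ² + (U² + ITU − TW − IV)τ²]

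Here IU − W = 36 and U² + ITU − TW − IV = 90. Take σ² = (1 − ICC)p(1 − p)/50 and τ² = ICC × p(1 − p), with p the control-phase rate, and a two-sided 0.05 test (two-sided is assumed).

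*The plan's own figure first.* For 50% to 65% at ICC 0.1, σ² = 0.0045 and τ² = 0.025. Var = 9 × 0.0045 × 0.1045 / (0.162 + 2.25) = 0.001755, so SE = 0.0419. Then 0.15/0.0419 − 1.96 = 1.62, which is power 0.95. At ICC 0.3 it is 0.98. The stated power of at least 0.85 holds as a lower bound.

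*Recording-only shifts, no change in care:*

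| Apparent gain | SE, ICC 0.1 / 0.3 | Probability of significance, ICC 0.1 / 0.3 |
|---|---|---|
| 3 points | 0.0415 / 0.0369 | 0.11 / 0.13 |
| 6 points | 0.0418 / 0.0372 | 0.30 / 0.36 |
| 12 points | 0.0419 / 0.0373 | 0.82 / 0.90 |

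These illustrate sensitivity to the assumption. They do not predict what the trial will find.

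**The case against.** The case on the other side has force on several points.

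- **Silence is not absence.** A reader might infer that nobody looks at any protocol. The article describes no verification of the questionnaire but does not rule it out, and a condensed article may leave such procedure to a fuller document. Only 'no check described' is supported.
- **A new protocol is a true 'yes'.** The structure indicators are defined as availability. If the strategy causes a protocol to be written, the score rises correctly.
- **The direction of self-report bias is not fixed.** The Discussion says all hospitals are legally obliged to implement the guidelines, so there is a motive to answer 'yes' in control rounds too. Over-reporting at that stage would dilute the effect.
- **Seven of nine is not seven-ninths of the weight.** The sample size rests on the process indicators; each structure item gives one answer per hospital and round.
- **Record changes are conditional.** A reader might infer that the strategy rewrites the records behind both process indicators. Table 2 offers checklist changes as an example, and the digital one only as something that may happen if possible. The link is direct for the STOP bundle and merely inferred for antibiotic timing.
- **Documentation is partly a target.** The Background lists clinical documentation among the deficiencies that led to the guidelines, so better recording is not pure artefact.
- **Two mechanisms are involved.** A changed record form is a change of instrument, which blinding would not cure. The process evaluation already lists changing registration systems.

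All of this limits the point, but two things remain. The Discussion's example is a self-reported item, so it cannot support the claim it illustrates. And the process evaluation records system changes without linking them to the strategy's own checklists or to how the primary result is worded.

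**Conclusion.** The objectivity claim does not fit the article's own data sources. Seven of nine primary indicators are yes/no answers from the unblinded hospital's contact person, with no check against a document described. Recorded STOP-bundle completion can rise at cross-over partly through better recording, and the planned model cannot separate that from the treatment effect.

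The size is unknown. The 3, 6 and 12 points rest on assumed true completion of 60%, full recording afterwards and every hospital changing its forms; partial uptake makes them smaller. Only the largest falls inside the 10% to 15% effect in the Power calculation section.

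A reader might go further and conclude that the trial would declare improved adherence when care had not changed. The documents do not support that: they show neither that record forms will change everywhere nor how complete recording was beforehand. This is a cheap improvement to measurement and wording, not a flaw that invalidates the design.

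**What to change.** 1. **Evidence for each structure 'yes'.** Score 'yes' only when the contact person supplies the dated protocol, regulation or registry evidence valid for that round. This is at most 7 items per hospital and round, so 7 × 9 = 63 per round and 63 × 4 = 252 over the trial. The cost is some collection and checking work, and a few 'yes' answers may become 'no'.
2. **Wording.** Replace the objectivity claim in the Discussion with a statement that the structure indicators are self-reported and the process indicators measure documented adherence. Word the primary conclusion as documented adherence. This costs only text.
3. **Descriptive report of recording changes.** From the process-evaluation log, report which hospitals changed checklists or record forms, and when. Make sure the log covers changes made by the strategy itself.

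Do not drop hospital-rounds after a form change, and do not let the conclusion depend on such an exclusion. It would remove only intervention cells in which a standard-package component was delivered. Table 1 has 18 intervention cells (9 hospitals, half of 36 hospital-rounds). If every hospital changed a form on crossing over, none would remain and no effect could be estimated. If some remained, a smaller estimate could not tell artefact from the genuine effect of that component.
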